### Moderator analyses

Moderator analyses will be conducted to investigate whether certain groups respond differently to the interventions. In addition to the potential mediators listed above, we will examine the impact of number of intervention sessions attended. Potential mediators and moderators of the intervention will be examined using mixed linear models or structural equation modelling, as appropriate.

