**Methods:**

We are conducting a randomised controlled trial to evaluate two early parenting interventions for mothers of children aged between 30 and 42 months in a Brazilian city. The first of these, dialogic book-sharing (DBS), aims to promote child cognitive and socio-emotional development; and the second, the ACT Raising Safe Kids Program (ACT), is designed to reduce harsh parenting. These interventions are being compared with a control group receiving neither intervention. Three hundred and sixty-nine families in a birth cohort are being randomly allocated to one of the three groups (DBS, ACT, Control). Facilitators deliver the interventions to groups of five to 10 mothers at weekly sessions for 8 weeks in DBS and 9 weeks in ACT. Independent assessments of parenting and child development are being made before the interventions, shortly afterwards, and at follow-up 6 months later. The primary outcome is child aggression, and the two main secondary outcomes are: (1) child cognitive and socio-emotional development and (2) harsh parenting. Longer-term outcomes will be investigated as the birth cohort is followed into late childhood, adolescence, and adulthood.

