## Methods

### Study design

The study is a three-arm RCT. The three arms are:Dialogic book-sharing (DBS) – a parenting intervention designed to promote sensitive and supportive interactions with children over picture books with the aim of improving child cognitive development and social understandingACT: Raising Safe Kids Program (ACT) – a parenting intervention designed to reduce harsh parenting; andControl group – this group receives no intervention input from the research team, but continues to receive the standard support services available to the community from which the sample is drawn

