### Recruitment and randomisation

Having identified the eligible sample, each family is being contacted by a recruiter in their own home. The study is explained to the mother who is then invited to take part.

From the 2015 cohort, 770 children met all the initial inclusion criteria above before being contacted in their homes. This sample was divided into 11 localities, each comprising approximately 70 families. Within each area, families are being invited to participate in the study (after confirming eligibility) in order of proximity to the intervention centre. Then, following consent and baseline evaluation, mother-child pairs are being randomised to one of the three study groups. This is being effected centrally (i.e. from the Federal University of Pelotas Centre for Epidemiological Research), minimising for child age, sex, level of harsh parenting at age 2 years, and child aggression at age 2 years (all binary variables). This process is being repeated serially across the 11 areas. The interventions are being delivered within public nursery/primary schools within each recruitment area. Assessments are being made at the Federal University of Pelotas Centre for Epidemiological Research (Fig. 1).

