#### Retention

Provisions have been put in place to maximise participant retention. This includes texts and phone calls to remind participants of scheduled assessments and sessions, fridge magnets to remind participants of the scheduled time, snacks, travel funds, and small gifts as well as a raffle for each study arm with the prize of a tablet. To increase adherence in the interventions, the mothers are: (1) shown videos about the benefits of the interventions, spoken by local mothers who had previously completed them, (2) taken by van to attend the first session and other sessions where their home is far from the intervention centre, (3) given travel funds for attendance at each session, (4) given snacks and a small gift for the children, and (5) provided with childcare during the sessions.

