### Potential moderators

The following variables will be examined as potential moderators: parental education, parental mental health, domestic violence, and maternal and child stress, maternal harsh parenting, number of siblings, and child sex, age, and aggression.

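### Sessions attended is placed among the moderators, but it arises after randomisation and does not exist in Control, so the stated models give only a confounded within-arm association

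*Protocol article*

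**What the plan says.** The Moderator analyses section states its purpose as "Moderator analyses will be conducted to investigate whether certain groups respond differently to the interventions". It then adds attendance to the variables already listed: "we will examine the impact of number of intervention sessions attended". The method is given in one sentence: "Potential mediators and moderators of the intervention will be examined using mixed linear models or structural equation modelling, as appropriate".

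Four other places bear on this:

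- **Recruitment and randomisation:** "following consent and baseline evaluation, mother-child pairs are being randomised to one of the three study groups". Every session therefore comes after allocation.
- **Study design**, on Control: "this group receives no intervention input from the research team".
- **Abstract, Methods:** "weekly sessions for 8 weeks in DBS and 9 weeks in ACT".
- **Potential moderators:** the list is "parental education, parental mental health, domestic violence, and maternal and child stress, maternal harsh parenting, number of siblings, and child sex, age, and aggression". All of these can be measured at or before baseline.

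Data analysis says that intervention effects are examined by intention to treat, adjusted for age, sex and baseline scores where applicable.

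**The concern.** A moderator analysis asks whether the difference between arms varies over levels of a characteristic. The characteristic must be observable in every arm and must not be affected by allocation. Attendance fails on both counts.

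Mothers who come to most sessions are likely to differ from those who come to few, and some of those differences may bear on child aggression. Domestic violence and parental mental health, both on the protocol's own moderator list, are plausible examples. The Retention section shows that the team expects circumstances to affect attendance: mothers are "taken by van to attend the first session and other sessions where their home is far from the intervention centre", and travel funds and childcare are provided.

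At stake is a secondary result. A slope of aggression on sessions attended could be read as evidence that more sessions work better, even if the programme did nothing.

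**Working it through.** **1. The plan's own figure.** The one design figure nearby is the 104 per arm under Sample size. With d = 0.45, two-sided alpha 0.025 and power 0.80, n = 2(2.2414 + 0.8416)²/0.45² = 94 per arm. Then 94 × 1.10 gives 104 and 94/0.90 gives 105. The figure reproduces and is not in dispute. The point below does not rest on it.

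**2. What can be identified.**

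| Requirement for a moderator | Attendance |
|---|---|
| Fixed before allocation | No: sessions follow randomisation |
| Observed in every arm | No: Control is offered none |
| Same scale across arms | No: maximum 8 in DBS, 9 in ACT |

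In Control, sessions attended is zero for everyone by design. The Control outcome therefore has no slope on attendance, and no interaction with arm can be estimated against it. A model with attendance as a covariate can use variation only within DBS and within ACT, and that variation is not randomised.

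**3. How large selection could be.** None of these inputs comes from the protocol except the sample size and the number of sessions.

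- n = 111: 369/3 = 123 per arm if equal, less 10% attrition (110.7).
- No effect of the programme or of any session.
- Unmeasured trait u, standard normal. Attendance is Binomial(9, p) with logit p = 0.8 + 1.2u. This implies a mean of 5.86 sessions, SD 2.35, and a correlation of 0.82 between trait and attendance.
- The trait correlates with aggression at r = 0.1, 0.2 or 0.3, more of the trait meaning less aggression.
- For the adjusted analysis, the trait is equally correlated with baseline aggression, and baseline to follow-up correlation is c = 0.5 to 0.7.

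Unadjusted, the expected 0-to-9 difference is -9 × 0.82 × r / 2.35. At r = 0.2 this is -9 × 0.82 × 0.2 / 2.35 = -0.63 SD. Adjusted for baseline, with k = 0.82r, it is -9 × k(1 - c) / [(1 - k²) × 2.35]. At r = 0.2 and c = 0.6, k = 0.164 and the result is -0.26 SD. Simulation (4,000 trials per setting) agrees and gives the rejection rates at two-sided 0.05:

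| r | Unadjusted, SD (false positives) | Adjusted, c = 0.5 | Adjusted, c = 0.6 | Adjusted, c = 0.7 |
|---|---|---|---|---|
| 0.1 | -0.31 (about 14%) | -0.16 (8%) | -0.13 (7%) | -0.10 (7%) |
| 0.2 | -0.63 (about 41%) | -0.32 (17%) | -0.26 (14%) | -0.19 (11%) |
| 0.3 | -0.94 (about 75%) | -0.50 (about 33%) | -0.40 (26%) | -0.30 (20%) |

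Repeat runs move the rates by one or two percentage points. At r = 0 the rate is the nominal 5%.

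**4. Cross-check with 8 sessions.** A separate unadjusted simulation with a somewhat weaker attendance model (logit p = 0.6 + 1.0u) gave -0.31, -0.60 and -0.91 SD from 0 to 8 sessions, with 13%, 36% and 67% false positives. The intention-to-treat difference stayed at about 0 throughout.

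**5. Over the usual range.** In the 9-session model only about 1.5% of mothers attend no session, and the interquartile range is 4 to 8. Over those 4 sessions the spurious difference is 4/9 of the values above: about -0.14 to -0.42 SD unadjusted and -0.04 to -0.22 SD adjusted.

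**The case against.** **The protocol states neither an interaction nor a causal dose claim, and a structural equation model could be a latent-class complier model.** This is true, and the analysis plan is not shown. But the protocol itself puts attendance under an effect-modification question and names no method that deals with selection. An analysis plan that handled attendance properly would have to reverse that placement, so this is more than missing detail.

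**The illustration is unfavourable to the plan.** Much of this stands. The unadjusted rates ignore the baseline adjustment stated under Data analysis. With it, the false-positive rates fall to roughly a quarter to a half of the unadjusted values at r = 0.2 and 0.3. A trait correlating 0.82 with attendance is close to a worst case, and the 0-to-9 contrast is largely extrapolation. The problem shrinks but does not vanish.

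**Stronger inferences.** A reader might conclude that the estimate reflects only who attends and nothing of what sessions do. The documents do not support that: the estimate mixes the two, and the stated models cannot separate them. A reader might also conclude that a false dose-response is certain, but it depends on confounding of unknown size. Nor does the protocol say that this analysis will set the exposure needed for scale-up. It discusses scale-up in terms of cost and non-specialist delivery, and plans no attendance threshold.

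**An instrumental estimate adds little.** This largely stands. With no sessions in Control, the per-session estimate is essentially the intention-to-treat difference divided by mean sessions. At a mean of 5.86 and a difference of -0.45 SD it would be -0.45/5.86 = -0.077 SD per session, with nearly the same test.

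**Conclusion.** The point holds as a fault in a stated secondary analysis. Attendance cannot serve as a moderator here, and the named models would return a confounded within-arm association. That conclusion rests on the design alone.

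The size is illustrative. With no true effect and a trait that strongly drives attendance, selection could produce about -0.3 to -0.95 SD between 0 and 9 sessions unadjusted, or about -0.10 to -0.50 SD after baseline adjustment. The upper adjusted value is comparable with the 0.45 on which the trial is powered, but it needs the strongest confounding considered and the full range of attendance.

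It would be wrong to infer that the trial's main conclusions are at risk: the intention-to-treat comparisons do not use attendance.

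**What to change.** 1. Remove sessions attended from Moderator analyses, and restrict moderators to the variables under Potential moderators, measured at or before baseline. The same sentence refers back to potential mediators where moderators seems meant; correct this too.
2. Estimate the effect of attendance with randomised arm as instrument for sessions attended, separately for DBS against Control and ACT against Control, with the primary model's covariates. State the exclusion restriction (allocation affects the outcome only through sessions) and the assumption of a linear effect per session. If a binary attendance definition is preferred, state it in advance; the restriction then also requires that attendance below it has no effect.
3. If a within-arm association of outcome with attendance is still reported, label it descriptive and non-causal.

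**Cost:** one additional analysis, needing only the attendance count and the outcomes already planned. Intervals will be wider than from the naive regression. The instrumental estimate mainly rescales the intention-to-treat effect and cannot establish the shape of a dose-response. No sample size or primary analysis changes.

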### Trial monitoring

#### Trial Steering Committee

An independent Trial Steering Committee (TSC) is monitoring the progress of the trial and advises the research team on matters arising during the course of the study. The PI (JM) consults with the TSC Chair once a month and the TSC meets biannually. The TSC is chaired by [name] (Chair), Department of Psychology, University of Cape Town. Other external academic representation is provided by [name], Institute of Criminology, University of Cambridge; [name], Division of Psychology and Language Sciences, University College London, and [name], Department of Psychiatry, Federal University of Rio Grande do Sul. [name], a mother of a child in 2015 Pelotas Birth Cohort Study (not selected for the trial) represents the local Pelotas community. TSC members from The PIÁ Trial study team are JM and IS.

## Discussion

The PIÁ Trial is an evaluation of two parenting interventions, both with the potential to reduce risk for later offspring violence. The DBS intervention targets child cognitive function/social understanding, which is implicated in the development of persistent child aggression, itself a strong predictor of later violence. The ACT programme targets harsh parenting and maltreatment, also associated with child aggression and later violence. The interventions are being delivered to mothers of 30–42-month old children in the Brazilian city of Pelotas, a city with a high rate of socio-economic disadvantage and a very high level of violence. The interventions are being delivered by trained facilitators, during weekly sessions over 8–9 weeks, to small groups of mothers. The primary outcome of The PIÁ Trial is child aggression. The two main secondary outcomes are child language and harsh parenting. A number of other assessments are being made, both of parenting and of child developmental progress. Parental reports of child behaviour may be biased because parents are, of course, not blind to their intervention status. However, The PIÁ Trial also includes observational measures of child behavior and parenting, direct tests with children, as well as external data sources (records), reducing this bias.

A major strength of the trial is that it is embedded within a birth cohort study, and the intention is to follow-up the cohort, including the trial participants, over many years. Indeed, The PIÁ Trial will be one of the few studies of early parenting interventions aiming to assess offspring outcomes into adulthood, and perhaps the only early parenting trial aiming to investigate long-term impact on aggression through the life-course [74].

### Outcomes, outputs, and dissemination

Following receipt of the trial statistical report, we will disseminate the study findings in several ways. We will publish them in peer reviewed academic journals and in relevant professional journals. We will produce a summary of the project’s objectives, methodologies, and key findings, together with recommendations for policy and practice, which will appear on the Federal University of Pelotas University and Instituto Cidade Segura websites. We will also write a briefing paper for distribution to the local government of Pelotas and local and regional press.

## Trial status

At the point of submitting this manuscript to the journal (16 August 2018), 304 out of the final 369 participants in the sample had been recruited. This paper represents version one of the protocol (Additional file 1).

## Abbreviations

ACT: ACT Raising Safe Kids Program
APA: American Psychological Association
DBS: Dialogic book-sharing
HIC: High-income country
LMIC: Low- and middle-income country
PI: Principal investigator
PIÁ: Pelotas Trial of Parenting Interventions for Aggression
RCT: Randomised controlled trial
WHO: World Health Organization
